## Abstract

**Background:**

Growing evidence links household air pollution exposure from biomass-burning cookstoves to cardiometabolic disease risk. Few randomized controlled interventions of cookstoves (biomass or otherwise) have quantitatively characterized changes in exposure and indicators of cardiometabolic health, a growing and understudied burden in low- and middle-income countries (LMICs). Ideally, the solution is to transition households to clean cooking, such as with electric or liquefied petroleum gas stoves; however, those unable to afford or to access these options will continue to burn biomass for the foreseeable future. Wood-burning cookstove designs such as the *Justa* (incorporating an engineered combustion zone and chimney) have the potential to substantially reduce air pollution exposures. Previous cookstove intervention studies have been limited by stove types that did not substantially reduce exposures and/or by low cookstove adoption and sustained use, and few studies have incorporated community-engaged approaches to enhance the intervention.

**Methods/design:**

We conducted an individual-level, stepped-wedge randomized controlled trial with the *Justa* cookstove intervention in rural Honduras. We enrolled 230 female primary cooks who were not pregnant, non-smoking, aged 24–59 years old, and used traditional wood-burning cookstoves at baseline. A community advisory board guided survey development and communication with participants, including recruitment and retention strategies. Over a 3-year study period, participants completed 6 study visits approximately 6 months apart. Half of the women received the *Justa* after visit 2 and half after visit 4. At each visit, we measured 24-h gravimetric personal and kitchen fine particulate matter (PM_2.5_) concentrations, qualitative and quantitative cookstove use and adoption metrics, and indicators of cardiometabolic health. The primary health endpoints were blood pressure, C-reactive protein, and glycated hemoglobin. Overall study goals are to explore barriers and enablers of new cookstove adoption and sustained use, compare health endpoints by assigned cookstove type, and explore the exposure-response associations between PM_2.5_ and indicators of cardiometabolic health.

**Discussion:**

This trial, utilizing an economically feasible, community-vetted cookstove and evaluating endpoints relevant for the major causes of morbidity and mortality in LMICs, will provide critical information for household air pollution stakeholders globally.

**Trial registration:**

ClinicalTrials.gov Identifier NCT02658383, posted January 18, 2016, field work completed May 2018. Official title, “Community-Based Participatory Research: A Tool to Advance Cookstove Interventions.” Principal Investigator [name]. Last update posted July 12, 2018.

**Electronic supplementary material:**

The online version of this article (10.1186/s12889-019-7214-2) contains supplementary material, which is available to authorized users.

## Background

### Background and study aims

Household air pollution is a major global health problem, as nearly 3 billion people rely on the burning of solid fuels (e.g., wood, charcoal) for cooking [1]. The combustion of biomass fuel in inefficient and poorly vented cookstoves creates a complex mixture of pollutants, which includes particulate matter (PM), carbon monoxide, volatile organic compounds, polycyclic aromatic hydrocarbons, and nitrogen oxides [2, 3]. Households cooking with biomass fuels experience PM_2.5_ levels (fine particles < 2.5 μm in aerodynamic diameter) 10 to 50 times higher than the World Health Organization’s current guideline of 25 μg/m^3^ for a 24-h mean [4, 5]. Household air pollution was estimated to cause 60 million disability-adjusted life years and 1.6 million premature deaths globally in 2017 [6].

Despite being a leading risk factor for morbidity and mortality worldwide, a complete understanding of the burden from household air pollution is unknown, as only a limited number of health outcomes are included in global burden estimates. Estimates of cardiovascular-related outcomes are almost entirely extrapolated from exposure-response effects associated with other sources of combustion-related pollution, such as active smoking, secondhand smoke, and ambient air pollution [6]. Growing evidence links household air pollution with increased risk for cardiovascular diseases (CVDs) through potential inflammatory and oxidative stress pathways [7–13]. Exposure to household air pollution is also gaining recognition for its potential impact on type 2 diabetes, with proposed mechanisms linking air pollution and metabolic dysfunction through chronic inflammation [14]. Further investigation is needed to more accurately characterize the burden of disease from household air pollution, particularly its impact on cardiometabolic diseases, which are among the leading causes of global morbidity and mortality [6].

Ideally, the solution to elevated household air pollution exposure is to transition households to clean cooking, such as with electric or liquefied petroleum gas stoves. However, those unable to afford or access these options will continue to burn biomass for the foreseeable future. Solid-fuel cookstoves designed with engineered combustion chambers and chimneys have the potential to reduce emissions and evidence suggests that the introduction of these stoves is capable of improving health. For example, the first randomized controlled trial evaluating the health impact of a chimney stove demonstrated a reduction in severe childhood pneumonia in Guatemala [15]. The intervention in Guatemala also resulted in clinically meaningful reductions in blood pressure levels among women [7]. Despite the potential to reduce household air pollution and improve health, the majority of cookstove programs (i.e., programs disseminating clean stoves and cookstoves designed to burn solid fuels more efficiently) around the world have not demonstrated consistent evidence for health-related benefits [16]. Achievable exposure reductions depend largely on a wide range of factors influencing adoption and sustained use of a newly introduced cookstove, including cultural, financial, geographical, familial, and individual [17, 18]. Low acceptance of new cookstoves, resistance to change cooking behaviors, inability of new stoves to meet the needs of the family, and continued use of traditional cookstove technologies have been observed across numerous cookstove interventions [17, 19–21]. While difficult to achieve in reality, near-complete displacement of traditional cookstoves is considered necessary to maximize health benefits [22, 23].

In our 2015 cross-sectional study among women in the same rural Honduran target population, we observed that 24-h mean kitchen and personal PM_2.5_ concentrations were 61 and 47% lower, respectively, among *Justa* cookstove users (i.e., engineered combustion zone and chimney stoves) compared to traditional cookstove users [24]. According to a simulated liquified petroleum gas stove intervention that assumed PM_2.5_ concentrations were reduced to 70 μg/m^3^, our 24-h *Justa* cookstove PM_2.5_ concentrations (average [median, IQR] personal PM_2.5_ concentration was 66 μg/m^3^ [53, 39 to 81 μg/m^3^]) [24] were within a range that should confer health benefits, particularly for systolic blood pressure [25]. Our cross-sectional measures of household air pollution were associated with elevated blood pressure (e.g., adjusted mean systolic blood pressure was 2.5 mmHg higher (95% confidence interval [CI], 0.7–4.3) per unit increase in natural log-transformed kitchen PM_2.5_), with suggestive evidence of associations when stove type (i.e., *Justa* compared to traditional cookstove use) was the exposure of interest [26]. We further observed cross-sectional effects of household air pollution on increased prevalence of metabolic syndrome (prevalence ratio per interquartile range increase in kitchen PM_2.5,_ 1.16 [95% CI, 1.0–1.3]) [24] and prediabetes/diabetes (prevalence ratio per interquartile range increase in kitchen PM_2.5_, 1.49 [95% CI, 1.1–2.0]); results were generally in the hypothesized direction for glycated hemoglobin (HbA1c) [27]. However, no evidence of association was observed with these outcomes when stove type was the exposure of interest [27]. Finally, there was evidence for a greater prevalence of self-reported symptoms (i.e., an indicator of quality of life) among traditional cookstove users compared to *Justa* users [28].

Despite the observed effects of household air pollution on cardiometabolic disease indicators from our formative study, residual confounding and lack of temporality are major limitations to cross-sectional designs, calling for the need for a randomized study with repeated measures of exposure and health outcomes. Although evidence suggests improvements in health following reductions in ambient air pollution exposures, much less is known about whether or not efforts to reduce exposures to emissions from household solid fuel combustion will result in health benefits, and if certain subgroups of the population are more likely to see improvements [29]. Furthermore, a better understanding is also needed on the barriers surrounding cookstove adoption and sustained use [18]. We propose that sustained use of a carefully selected, culturally appropriate, wood-burning cookstove with an engineered combustion chamber and chimney (the *Justa* cookstove) will result in lower air pollution exposures and better health status compared to the use of the traditional cookstove. Within a community-engaged framework among rural Honduran women, this cookstove intervention addresses the following aims through an individual-level, stepped-wedge randomized controlled trial:

### Aim 1: in an intent-to-treat framework, evaluate the impact of the *Justa* cookstove intervention on indicators of cardiometabolic disease risk

Among 230 female primary cooks, we will evaluate 3 primary health endpoints (blood pressure, C-reactive protein [CRP], and HbA1c) among those randomly assigned to using traditional and *Justa* cookstoves during a 3-year project with 6 study visits, spaced approximately 6 months apart. Secondary health endpoints include indicators of other cardiometabolic- and respiratory-related outcomes, specifically metabolomics and other biomarkers of systemic injury and inflammation from dried blood spots, augmentation index, central pulse pressure, blood lipids, self-reported health symptoms, fractional exhaled nitric oxide, and telomere length from buccal cells. We will evaluate the potential for effect modification by age, blood pressure, diabetes, body mass index (BMI), waist circumference, and metabolic syndrome. *We hypothesize that use of the Justa cookstove (intervention) will result in improved indicators of non-communicable disease risk as compared to use of the traditional cookstove among Honduran women.*

### Aim 2: in an exposure-response framework, characterize the associations between household air pollution measurements and indicators of cardiometabolic disease risk

To explore the link between exposure to household air pollution and indicators of cardiometabolic disease risk, we will utilize a longitudinal design with 6 repeated measures of 24-h kitchen and personal PM_2.5_ and measures of primary and secondary outcomes (indicators of cardiometabolic- and respiratory-related outcomes as listed above in Aim 1) collected every 6 months over a 3-year study period among the 230 study participants. We will evaluate the potential for effect modification by age, blood pressure, diabetes, BMI, waist circumference, and metabolic syndrome. *We hypothesize a positive exposure-response relationship between PM*_*2.5*_
*and indicators of cardiometabolic- and respiratory-related outcomes. We expect the characterization of the exposure-response to be transferable to other settings/stove types; thus providing the potential to inform decisions of acceptable levels of household air pollution regardless of cooking technology.*

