For the exposure-response analysis, we will use a linear mixed model similar to the model used in the intent-to-treat analysis. In this framework, the personal and kitchen PM_2.5_ measurements will be included as the exposure variable *x*_*ij*_ in Eq. (1). As the exposure-response approach will not utilize the study’s randomization to control for confounding, potential confounders identified a priori will be included in Eq. (1) as additional fixed effect terms. Potential confounders include participant age, indicators of socioeconomic status (e.g., household possessions, participant education level, beds per person in each household), physical activity levels, BMI, and dietary intake. We will also conduct a “per protocol” analysis using self-reported actual cookstove use, rather than assigned cookstove.

We will evaluate effect modification by adding the following variables as interaction terms with the stove assignment or exposure measurement variable in separate models: age (< 40 or ≥ 40 years), blood pressure (normal systolic < 120 and diastolic < 80 vs. borderline high/high systolic ≥ 120 or diastolic ≥ 80), diabetes status (normal hbA1c < 5.7% vs. pre-diabetic/diabetic ≥ 5.7%), BMI (normal < 25 or overweight/obese ≥ 25), waist circumference (< 80 cm vs. ≥80 cm), and metabolic syndrome (presence vs. absence).

Sensitivity analyses will be conducted to assess the impact of different forms of the adjustment for time in Eq. (1) by varying the number of spline functions and considering alternative representations such as indicators of season or visit number. We will also conduct sensitivity analyses that exclude women who were taking medications that could influence inflammation in the body, such as hypertension or vitamins, or who were ill at the time of the health measurements. Additional sensitivity analyses will exclude air pollution samples that came from pumps that ran for less than 24 h, and flow rates that strayed outside the 10% pre- and post-sampling range.

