### Limitations

Several limitations are important to note. While traditional stoves in women’s homes were destroyed before *Justa* construction, secondary traditional stoves could be easily remade. We anticipate that exclusive use of *Justa* cookstoves for the full study period would be difficult to achieve, as families in this region often relied on secondary stoves to cook for holidays or large family gatherings, boil corn in large pots for tortillas, and roast coffee beans. Women were not excluded from the study if they continued using traditional cookstoves after the *Justa* intervention. Near-complete displacement of traditional stoves is considered necessary to see health benefits [23], and our PM_2.5_ levels from *Justa* users will likely remain above the WHO guideline of 25 μg/m^3^ for a 24-h mean in many of the households [4].

A major limitation of this study was that blinding for participants and field team members was not possible given the type of intervention. An additional limitation to this study is our lack of ambient air pollution data that might affect women’s longer-term exposures, such as emissions from burning agricultural fields, neighbors’ biomass combustion, diesel traffic fumes, and trash burning. We attempted to capture these additional sources of exposure in the questionnaires at each visit to control for these co-occurring exposures during analysis.

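### Aim 2 expects a PM2.5 slope that transfers across stove types, but the stated model gives one pooled slope and never checks whether it differs by stove

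*Protocol article*

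**What the plan says.** Aim 2 states the expectation "We expect the characterization of the exposure-response to be transferable to other settings/stove types" and the use it is meant for: "thus providing the potential to inform decisions of acceptable levels of household air pollution regardless of cooking technology". For effect modification the same aim says "We will evaluate the potential for effect modification by age, blood pressure, diabetes, BMI, waist circumference, and metabolic syndrome", which is six participant characteristics.

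In Statistical analysis, for Aim 2 "we will use a linear mixed model similar to the model used in the intent-to-treat analysis", and the personal and kitchen PM2.5 "measurements will be included as the exposure variable" in Eq. (1). That position held assigned stove in the intent-to-treat model. On covariates, "Potential confounders include participant age, indicators of socioeconomic status", followed by physical activity, BMI and diet. The modifiers are entered "as interaction terms with the stove assignment or exposure measurement variable in separate models". The sensitivity analyses vary the form of the time adjustment, exclude women on certain medications or ill at measurement, and exclude deficient air samples. The per-protocol analysis substitutes self-reported for assigned stove; it is not described as being fitted together with PM2.5.

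Limitations states that "blinding for participants and field team members was not possible given the type of intervention".

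**The concern.** Transfer across stove types has a consequence that this trial can check: the slope should be the same under its own two stove conditions. Stove is absent from the confounder, modifier and sensitivity lists of the PM2.5 model, so no stated analysis makes that check.

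Stove assignment also drives the exposure. The Background reports PM2.5 in Justa users 61% lower in kitchens and 47% lower for personal samples. If a new stove affects an outcome by any route other than PM2.5, a model without a stove term assigns part of that effect to PM2.5. The clearest such route is knowing that one has the new stove. It matters most for the self-reported symptoms, which are secondary endpoints covered by Aim 2 and are asked about partly in relation to cooking.

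At stake is a slope offered for setting acceptable pollution levels under other technologies. It could be inflated, or could average two different slopes, with nothing in the planned output to show it.

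**Working it through.** **Inputs from the protocol article.** Table 1: 115 women per arm, six visits, Justa at four visits in arm 1 and two in arm 2, so (115×4 + 115×2)/(230×6) = 690/1380 = 50% of scheduled person-visits. Statistical analysis: SD 12 mmHg, within-person correlation 0.76, 10% loss, 80% power at 1.81 mmHg. Background: PM2.5 lower by 61% (kitchen) and 47% (personal); personal IQR 39 to 81 μg/m³ in Justa users; formative slope 2.5 mmHg per ln unit of kitchen PM2.5.

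**Assumptions not in the article.** Two-sided 5% level; PM2.5 on the log scale; linear time trend; SD of ln PM2.5 within stove 0.54 to 0.8; within-woman correlation of ln PM2.5 0.2 to 0.5; a non-smoke stove effect of -1.81 mmHg, for illustration only.

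**1. The plan's own figure.** With 115 × 0.9 = 103.5 women per arm, the generalised least squares SE of the stove coefficient is 0.650 mmHg. Detectable difference: (1.96 + 0.84) × 0.650 = 1.82. Power at 1.81: Φ(1.81/0.650 - 1.96) = 79.5%. The stated 80% is reproduced.

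**2. How far stove drives PM2.5.** Contrasts: ln(0.39) = -0.94 (kitchen), ln(0.53) = -0.635 (personal). SD of ln personal PM2.5: ln(81/39)/1.349 = 0.54. Stove share of its variance: 0.25×0.635²/(0.25×0.635² + 0.542²) = 0.26.

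**3. No smoke effect, non-smoke stove effect of -1.81 mmHg** (simulation, 208 women × 6 visits). Full absorption would give 1.81/0.635 = 2.85 (personal) or 1.81/0.94 = 1.93 (kitchen) mmHg per ln unit.

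| PM2.5, SD of ln PM2.5 | Mean pooled slope | Share of full absorption | False positives |
|---|---|---|---|
| Personal, 0.54 | +0.35 to +0.52 | 12 to 18% | 16 to 22% |
| Kitchen, 0.54 | +0.42 to +0.58 | 22 to 30% | 25 to 34% |
| Personal, 0.8 | +0.16 to +0.25 | 6 to 9% | not tabulated |
| Kitchen, 0.8 | +0.23 to +0.34 | 12 to 18% | not tabulated |

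With a stove term the mean slope lies within 0.02 of zero, and false positives (SD 0.54) are 4.6 to 6.3%. The slope SE rises by 3% (0.245 to 0.252) to 20% (0.384 to 0.462).

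**4. Slopes that differ.** With 2.5 under traditional and 0.5 under Justa, the pooled model returns 1.26 to 1.39, which describes neither stove. An interaction term estimates the difference at about -2.0 with SE 0.67, three SEs from zero.

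**5. What the interaction can detect.** Its SE is 0.45 to 0.67, so 80% power needs a difference of 2.80×0.45 = 1.26 to 2.80×0.67 = 1.88, roughly 1.3 to 1.9 mmHg per ln unit.

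**6. Stove adjustment when smoke explains everything.** True slope 2.5, no non-smoke effect, kitchen contrast 0.94; the 24-h sample carries error of SD 0.4 to 0.6 around longer-term exposure, whose own within-woman SD is 0 to 0.4 (both assumed). The pooled slope is about 0.50 to 1.52, the adjusted slope about 0.10 to 1.29, and a spurious stove coefficient of about -1.2 to -2.3 mmHg appears. Adjustment discards the randomised contrast and leaves the variation in which sampling error weighs most.

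**The case against.** The strongest case against has five parts.

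- **Only an expectation, in a condensed article.** Aim 2 is worded as exploration, the confounder list is not closed, and further models could sit in an analysis plan that is not shown. This lowers the weight of the point. But the article itself sets out the claim, the model, the modifiers and the sensitivity analyses, and stove is missing wherever it would be needed to examine the claim.
- **No documented non-smoke effect.** This is true. The -1.81 mmHg is illustrative, and if the stove acts only through PM2.5 there is no confounding of this kind. The formative metabolic results, associated with PM2.5 but not with stove type, give no support for a direct stove effect. The plan relies on its absence without testing it.
- **Absorption is partial.** A reader might infer that the pooled slope would carry the whole stove effect, or be merely an artefact of it. Step 3 shows 6 to 30% of full absorption.
- **Work effort is largely covered.** A reader might also infer that reduced wood cutting or cooking would be credited to PM2.5. Under Additional data both enter the physical activity score, and physical activity is a listed confounder. Knowledge of the new stove is not covered in this way.
- **The stove-adjusted slope is no arbiter.** A reader might want transferability claimed only if the pooled and adjusted slopes agree. Step 6 shows why that rule is unsound. This objection stands in full and shapes the fix.

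**Conclusion.** The point holds in limited form. The stated Aim 2 analysis cannot show whether the PM2.5 slope differs between traditional and Justa stoves, and it would partly absorb any stove effect not acting through PM2.5. For systolic pressure the illustrated bias is about +0.2 to +0.6 mmHg per ln unit for a -1.81 mmHg non-smoke effect, against a formative slope of 2.5. It would be zero if there were no such effect. These sizes depend on the assumed variance components of PM2.5 and do not carry over numerically to the symptom outcomes.

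The documents do not show that a non-smoke effect exists or that the pooled slope is wrong. Nor can the trial settle transfer to other fuels or settings: both conditions burn wood, and the traditional group ranges from open fires to modified stoves with chimneys. The most it can support is consistency between its two stove groups.

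**What to change.** 1. Add assigned stove type to the listed effect modifiers of the PM2.5 models, and report the PM2.5-by-stove interaction with its confidence interval. A non-significant interaction should not be read as proof of equal slopes.
2. Report a stove-adjusted PM2.5 model beside the pooled one as a sensitivity analysis, with a note that adjustment removes the randomised exposure contrast and worsens attenuation from 24-h measurement error. Do not make agreement of the two slopes a condition for any conclusion.
3. Reword Aim 2 so that its conclusion concerns consistency across the traditional and Justa wood stoves rather than any cooking technology.

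Cost: two extra models for each outcome and exposure measure, and no new data. The adjusted slope has an SE about 3 to 20% larger. The interaction can detect only slope differences of roughly 1.3 to 1.9 mmHg per ln unit, under the assumed PM2.5 variance, so its interval may be too wide to exclude differences that matter.
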